**1. INTRODUCTION**

Parkinson’s disease (PD) is the second most common neurodegenerative disease, which affects at least 70,000 Australians and is increasing in occurrence with an aging population. Currently there is no cure and very few options to treat symptoms, with the exception of levodopa whose effects are temporary. It is proposed in this trial to test the effectiveness of photobiomodulation treatment (PBMt) to alleviate some of the symptoms of PD and improve quality of life. PBMt entails the delivery of non-thermal light (either laser or LED) as a therapy. PBMt has a proven track record to reduce pain, accelerate healing and reduce inflammation. More recently PBMt has undergone trials to assess its affect in the treatment of stroke, depression, traumatic brain injury and Alzheimer’s disease. The proposed Phase 1 trial follows on from two other completed trials using PBMt to treat the symptoms of PD; one in Brisbane and one in Adelaide.

**2. BACKGROUND**

Parkinson’s Disease (PD) is the second most common neurological disease and refers to a progressive neurodegenerative disorder (i.e., degeneration of the nervous system). Clinical manifestations in people with PD are altered muscle tone, bradykinesia (slowness of movement), choreatic movement (constant writhing), rigidity (increased muscle tone during movement), akinesia (difficult in initiating and stopping movement) and resting tremor (shaking movements). The prevalence of PD in Australia is approximately 70,000 with 32 new cases diagnosed every day resulting in a very substantial total economic cost to the Australian community of $9.9b per annum (Deloitte Access Economics, 2015).

PD presents as a result of nerve cell loss in an area of the midbrain (the substantia nigra) (Calabresi et al, 2015). In humans, it is estimated that when motor (movement) signs first appear and a diagnosis is possible, there is already a 27% loss of dopamine nerve cells.

The cause of PD is unclear. Some evidence suggests that it may be caused by exposure to a neurotoxin or defective genes. Another hypothesis is associated with dysfunction of the powerhouse of the cell, the mitochondria. It is within the mitochondria that cellular energy is created by the production of adenosine triphosphate (ATP). ATP is the fuel for all cellular (including nerve) function. Under certain conditions there can be a progressive accumulation of mutations in mitochondrial DNA that reduces mitochondrial efficiency and ATP yield. This process leads to an increase in toxic elements (reactive oxygen species), generating oxidative stress and subsequent nerve degeneration (Calabresi et al, 2013; Fuhrer et al, 2014).

The current medical treatment for PD is dopamine replacement drug therapy. In some cases, more radical management, such as implantation of deep brain stimulation (DBS) can be offered (Calabresi et al., 2013). Dopamine drug therapy (DDT) aims to replace the dopamine lost from the system, while DBS aims to introduce stimulation to basal ganglia pathways impaired by the loss of the dopamine.

DDT, although effective in assisting communication between cells in the impaired mid brain (Calabresi et al., 2015) has many side effects, (more common in the medium term) that may cause alterations in other neural pathways (Ferrazzoli 2016). Identifying alternative non-invasive methods of stimulating cellular activity in neurones within the impaired mid-brain may prove highly beneficial to people with PD.

Physiotherapy has been established as an effective and complementary treatment for the management of PD regardless of medical interventions (Tomlinson et al., 2013). The aim of physiotherapy is to offer strategies and improve strength and capacity for some of the impairments such as gait disturbances, reduced strength, coordination and balance responses, assist in movement initiation strategies and maintain dexterity and fine motor control. Current physiotherapy, therefore, does much to improve the quality of life and functional capacity, however, it is unable to halt disease progression.

Photobiomodulation therapy (PBMt; also known as light therapy, low intensity laser therapy or low-level laser therapy) has been used in humans for a wide range of conditions such as musculoskeletal disorders, inflammatory conditions and neurogenesis. PBMt is a safe, non-invasive, and non-thermal modality that is based on a substantial body of research dating back to the 1960s (Chung, 2012). The mechanisms of action are proposed to involve the stimulation of mitochondria by the absorption of photons in cytochrome c oxidase, resulting in increased ATP production, leading to reduced oxidative stress, anti-inflammatory effects, improved cellular energy, increased synthesis of enzymes, and increased focal cerebral blood flow (Hamblin, 2016). Most encouragingly, recent research has reported neuroprotection against brain cell degeneration, stimulated by PBMt in animal models of PD (Darlot et al, 2016; Johnstone et al 2014, Johnstone et al, 2015).

To date, the basic science research, and anecdotal clinical evidence offer support for the benefits of PBMt in PD (Shaw et al 2012; Johnstone et al 2014, Johnstone et al, 2015; Darlot et al, 2016). In a monkey model in which a Parkinson’s Disease state was induced by a neurotoxin, the application of PBMt reduced the signs of motor dysfunction as well as promoted neural protective responses and in some cases neuro-regeneration of impaired nerve cells (Darlot et al, 2016). Further research, reports PBMt is well tolerated and may be valuable in improving sleep-wake cycles in patients with PD (Videnovic et al., 2017). PBMt has also been shown to be safe in other brain-related conditions. Studies have applied both transcranial (e.g., WARP-LED) or intracranial (e.g., optical fiber device) methods to deliver light therapy at power intensities ranging from 1–700 mW/cm^2^ and have reported no adverse effects on brain tissue structures and function (Moro et al, 2014; Hamblin, 2016; Saltmarche et al, 2017).

In the helmet experiment (Stone and Mitrofanis, 2012) one of the researchers in our team (JM) analysed the survival of dopaminergic neurones in the mouse brain (substantia nigra pars compacta) and showed that body-only PBMt exposure is effective in protecting dopaminergic centres of the brain, although less protective than head-and-body radiation. The protective effect of PBM may therefore be mediated partially by a systemic or indirect effect, involving quite different mechanisms to those involved in the transcranial effect (as being measured in the Brisbane arm of the study). The site of PBMt application need to be assessed to understand where it may be best in future to apply the therapy to optimise treatment.

The applicability of PBMt, the positive animal study responses and the lack of side effects suggest that PBMt could provide a viable adjunct to current treatments for PD. No study has yet explored this method of treatment in humans. We propose to trial the PBMt in a series of case studies to best identify the type of application, the site of application and dose rate that may produce positive changes in clinical signs and functional capacity of people with PD. Given that abscopal effects (where treatment in one part of the body can influence remote sites) are known for PBMt, our research seeks to understand whether site of PBMt application influences clinical signs and functional capacity of people with PD, in the same way that dosing may do. Hence, a Brisbane arm of our parallel studies (with separate HREC application) will evaluate the effect of PBMt to the head of eligible participants with PD whilst the Sydney arm will evaluate the effect of PBMt on the abdomen and spine. The abdomen is a critical site due to recent evidence proposing a link between the gut and brain associated with PD (Pellegrini et al, 2015). The spine as part of the central nervous system is a key site of application due to its links with the brain. This HREC application is specific to the Sydney arm of our parallel studies.

Investigators in our team have already established the efficacy and safety of PBMt in animals (rodents and primates) using an invasive technique (Darlot et al, 2016). Based on recent studies of transcranial PBMt in humans with traumatic brain injury, stroke and dementia, we know that it is not necessary to apply PBMt utilizing a surgical method. We intend to use a non-invasive remote site approach in order to measure any abscopal effect.

The Sydney proof-of-concept trial follows on from proof-of-concept trials which have been completed in Brisbane and Adelaide. The Brisbane trial was a randomised placebo trial using transcranial photobiomodulation and showed significant differences between the treated and placebo group. The Adelaide trial was a waiting-room design with transcranial, intranasal, cervical spine and abdominal photobiomodulation; results are still being analysed but look very encouraging, including potentially positive changes in the microbiome. The Sydney trial will be a case-matched trial and use abdominal and cervical spine photobiomodulation only. The Sydney trial will be conducted over a 12-week treatment period and will assess a number of outcome measures, including motor abilities, cognitive function, microbiome changes, cytokine levels and potential Parkinson’s disease marker changes, as well as self and carer assessments of wellness. The trial is to be conducted in two stages: an initial cohort will be assessed in September, to begin treatment in October. A further cohort will begin treatment in August 2021. The funding for the Sydney trial has been provided by the San Foundation and from private donors. Additional funding ($27,000) has been obtained to conduct the second stage of the trial. The results from all three trials will be used to argue for a large-scale, randomised, double-blinded trial.

The idea for this study emerged after a previous study evaluating the application of photobiomodulation in participants with PD was completed (approved by Griffith University HREC). Ethics approval for this study is being sought through the AHCL HREC. This study will be a simplified blinded placebo/sham-controlled trial with the following sites:

- Northshore Musculoskeletal and Laser Physiotherapy Clinic, [name].
- Photobiomodulation Clinic, Specialist and GP Centre, San Hospital, [name]
- [name], San Hospital, [name]

The sponsor and the supplier of devices for this study will be SYMBYX Biome Pty Ltd, [name]

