**6. STUDY DESIGN**

Stage 2

Blinded, placebo/sham-controlled trial consisting of 40 participants. Group 1 (20 participants) will be

participants with Parkinson’s disease receiving treatment and Group 2 (20 participants) will be a placebo/sham-control group receiving no treatment. All groups will begin intervention in

August 2021. Treatment will consist of PBMt to the head and nose (either active or

placebo treatment), 3 times per week for 12 weeks. Outcome measures to be collected by Specialist

Examiners and the Physiotherapists.

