**12. STUDY PROCEDURES**

**11a. Study procedure**

The PBMt intervention will consist of 3 treatment sessions per week for 12 weeks (Groups 1). Participants in the active treatment group will receive transcranial light treatment with a PDNeuro LED helmet device (parameters given in Appendix 1). The treatment areas are 20 points (

154.5 joules total energy). The treatment time is 24 minutes. Participants in the placebo/sham group (Group 2) will receive the same apparent treatment as Group 1, except that they will be “treated” with sham transcranial LED devices that delivers no light.

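### The protocol contradicts itself on where the light is applied: the Background says abdomen and cervical spine only, while the design, procedure, device and contingency sections treat only the head and nose, which leaves the remote-effect question and the treatment-site comparison unsupported.

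*Protocol*

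**What the plan says.** Protocol section 2 (Background) describes parallel studies that differ by treatment site, with the head assigned to Brisbane. For this trial it says that "the Sydney arm will evaluate the effect of PBMt on the abdomen and spine" and identifies the document with that arm: "This HREC application is specific to the Sydney arm of our parallel studies". The scientific purpose is given as "We intend to use a non-invasive remote site approach in order to measure any abscopal effect". Later in the same section: "The Sydney trial will be a case-matched trial and use abdominal and cervical spine photobiomodulation only".

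The operative sections describe something else:

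- Section 6 (Study Design, headed Stage 2): "Treatment will consist of PBMt to the head and nose".
- Section 11a (Study procedure): "Participants in the active treatment group will receive transcranial light treatment with a PDNeuro LED helmet device". The sham is also a transcranial device.
- Appendix 1 (device specification): 20 transcranial LED locations and one nasal LED.
- Appendix 8 (contingency protocol): home treatment, again to the head and nose.

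Two further sections use the treatment site as an analytic contrast. Section 13b plans chi-square comparisons of Sydney with Brisbane and Adelaide to find the best areas to treat. Section 15 says that the results will show which site of application, if any, influences outcome.

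**The concern.** A protocol has to identify its intervention without ambiguity, and this one names two that do not overlap. The word only in the Background sentence on abdominal and cervical spine treatment rules out reading the helmet as an addition to it.

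The site also determines what the trial can conclude. A remote effect is one seen when light is applied away from the brain. Light delivered through the scalp and nose cannot separate a remote effect from a direct one. If the operative sections stand, the stated reason for treating Sydney differently from Brisbane disappears, and the cross-trial comparison loses the contrast on which it depends.

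**Working it through.** **1. Does the device specification leave room for any other site?** Inputs are the average powers and treatment times in Appendix 1. The formula is energy (J) = average power (W) × time (s).

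| LEDs | Power (W) | Time (s) | Recomputed (J) | Stated (J) |
|---|---|---|---|---|
| 660 nm, transcranial | 0.0712 | 12 × 60 = 720 | 51.26 | 51.3 |
| 810 nm, transcranial | 0.1034 | 12 × 60 = 720 | 74.45 | 74.4 |
| 810 nm, nasal | 0.020 | 24 × 60 = 1440 | 28.80 | 28.8 |
| Total | | | 154.51 | 154.5 |

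The plan's figure is reproduced. Transcranial light supplies 51.3 + 74.4 = 125.7 J and nasal light 28.8 J. The remainder for abdomen or spine is 154.5 − 125.7 − 28.8 = 0 J. This calculation confirms the LED list in the same appendix; it does not measure an effect on the trial's results. A small related mismatch is that section 11a attributes the full 154.5 J to the 20 points and does not mention the nose, although the total includes the 28.8 J nasal share.

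**2. The sections side by side.**

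| Section | Site stated for this trial |
|---|---|
| 2 (parallel-studies paragraph) | abdomen and spine |
| 2 (description of the Sydney trial) | abdomen and cervical spine, exclusively |
| 6 | head and nose |
| 11a | transcranial, active and sham |
| Appendix 1 | scalp and nose |
| Appendix 8 | head and nose |

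No abdominal or spinal device, treatment point or dose is given in the available text.

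**3. Does the Stage 2 label resolve it?** The Background says: "The trial is to be conducted in two stages: an initial cohort will be assessed in September, to begin treatment in October". It continues: "A further cohort will begin treatment in August 2021". August 2021 is also the start date in section 6, so the Stage 2 cohort is inside the Sydney trial that the Background describes. No change of site between stages is stated. The label does not resolve the conflict.

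**4. What happens to the cross-trial comparison?** From section 2, Brisbane was transcranial, and Adelaide combined head, nose, cervical spine and abdomen.

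| Trial | If Sydney is head and nose | If Sydney is abdomen and spine |
|---|---|---|
| Brisbane | head | head |
| Adelaide | all sites together | all sites together |
| Sydney | head and nose | abdomen and spine |
| Group with abdomen/spine alone? | none from this design | Sydney |

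Under the head-and-nose text, Sydney largely repeats Brisbane's site. Adelaide cannot isolate the abdomen or spine because its sites were treated together.

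**The case against.** The strongest reply is that the Background wording is left over from the first stage. Every operative section points to the head, and section 6 carries the Stage 2 label. The Background itself moves from calling the Sydney trial case-matched to describing a sham-controlled study, which looks like text from two periods. This is plausible. It also makes it less likely that staff would deliver the wrong treatment. But the document never says that the site changed, so this explains the contradiction without removing it. If an earlier abdomen/spine cohort exists, it might supply the missing group, but the protocol does not describe such a group or say that it will be used.

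The second reply concerns consequence, and it stands. The aim, objectives and hypotheses (sections 3 to 5) name no treatment site and do not mention an abscopal effect. A helmet-versus-sham comparison can address them. A reader might infer that the trial as a whole cannot answer its question; the documents do not support that.

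Two other inferences are tempting and also fail:

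- **That the microbiome hypothesis has lost its basis.** The Background justifies abdominal treatment by a gut–brain link, but nowhere ties the microbiome hypothesis to abdominal light. The microbiome signal it mentions came from Adelaide, where all sites were treated together. The hypothesis is already ranked tertiary, so nothing here requires it to be relabelled.
- **That a positive result would be credited to a site never treated.** This is speculation. The procedure and device sections would identify the helmet in any report.

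**Conclusion.** The contradiction is real, stands in current text, and must be reconciled. Two statements in the Background give one site; sections 6 and 11a and Appendices 1 and 8 give another, and the whole 154.5 J is assigned to scalp and nose.

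The consequence is limited to three places. If the head-and-nose text stands:

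- the abscopal question in section 2 cannot be answered;
- the search in section 13b for the best treatment area has no abdomen/spine-only group from the design described;
- the site conclusion in section 15 lacks the same support.

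The site-neutral main aim is not affected. The conclusion rests on reading section 2 as describing one Sydney trial that includes the August 2021 cohort, which is what its text says, and on taking the sites treated in Brisbane and Adelaide from that same section.

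**What to change.** The sponsor must reconcile section 2 with sections 6 and 11a and Appendices 1 and 8 so that one treatment site is stated throughout. This review does not say which site is right. The dependent claims then follow:

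- **If the head-and-nose text stands:** remove the abscopal claim from section 2, and remove from sections 13b and 15 the best-area and site conclusions that depend on an abdomen/spine arm. If the site changed between stages, say so in section 2. Align section 11a with Appendix 1 on the nasal share of the energy.
- **If the abdomen/spine text stands:** make the design, procedure, sham, device and contingency sections consistent with it.

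The first route costs amendment wording, notification of the ethics committee and a narrower stated conclusion, with no extra participants. The second costs more, because the specified active and sham devices are both transcranial.

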**8. STUDY POPULATION**

Two groups of participants will be recruited: 20 participants with PD receiving active intervention (Group 1) and 20 participants with PD receiving sham/placebo intervention (Group 2)

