**13b. Statistical analysis**

As a series of N=1 studies, it is anticipated that only basic statistical analysis will be performed. For each outcome measure, descriptive data (mean, standard deviation) will be calculated. From this data, “minimally important difference” (MID) scores will be computed based on ½ SD of each measure. This is a common MID measure (Norman et al, 2003) based on the distribution of the participant scores at baseline and provides a sensitive indicator of significant change over time for N=1 case studies. As such, it does not suffer from a lack of statistical power that would be evident with more traditional ANOVA approaches with small sample sizes. The number of participants showing improvement (i.e., difference between two time points > MID) can be compared between time points with chi-square analyses.

Participants showing improvement in the Sydney arm of the multi-centre Parkinson’s trial will be compared to the Brisbane and Adelaide arms (chi-square analysis) in order to establish optimum PBM areas of treatment and doses regimens.

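### The Background calls the trial case-matched, Section 6 calls it blinded and sham-controlled, and no readable section states random or concealed assignment, so the active-versus-sham comparison is not protected against selection bias.

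*Protocol*

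**What the plan says.** The protocol describes the design in several ways.

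- Section 2 (Background): "The Sydney trial will be a case-matched trial". The same sentence goes on to limit treatment to the abdomen and cervical spine.
- Section 2, next paragraph: "This study will be a simplified blinded placebo/sham-controlled trial".
- Section 6 (Study Design), under a Stage 2 label: "Blinded, placebo/sham-controlled trial consisting of 40 participants", with 20 active and 20 sham, treated at the head and nose.
- Section 2, earlier: "We propose to trial the PBMt in a series of case studies".
- Section 13b: "As a series of N=1 studies, it is anticipated that only basic statistical analysis will be performed".

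On how a person comes to be in Group 1 or Group 2, the protocol says very little. Section 8 says "Two groups of participants will be recruited" and gives the two group sizes. Section 10 names advertisements and clinician referral as the sources of participants. Section 12 describes the active and sham devices. Appendix 8 mentions group allocations once, when it explains how participants will be kept blind. The word randomised occurs only for the completed Brisbane trial and for a large trial that may follow.

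**The concern.** The aim in Section 3 is to determine efficacy, and the sham group is the only concurrent control. That comparison can be read causally only if assignment is unrelated to prognosis, and the protocol has to secure this before anyone is enrolled. It is not a detail that can wait for a statistical analysis plan.

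The one term in the readable text that bears on how the groups are formed is case-matched. That is a non-random principle, and no matching factors or procedure are given. Even if carried out well, matching 20 to 20 balances only the factors chosen. Severity, response to medication, motivation and other features could still differ between arms, and the difference could be read as a device effect. Blinding participants after assignment does not correct an imbalance that arose at assignment.

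The Background and Section 15 say that the results will be used to argue for and to power a larger trial, so a distorted contrast would carry forward.

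**Working it through.** **Step 1. Text check.** Each readable section was checked for an assignment method.

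| Section | Design label or content | Random sequence? | Concealment? | Matching factors? |
|---|---|---|---|---|
| 2, Background | case-matched; then blinded sham-controlled | no | no | no |
| 6, Study Design | blinded sham-controlled, 20 and 20 | no | no | no |
| 8 and 9, Population and Cohort | two groups | no | no | no |
| 10, Recruitment | advertisements and referral | no | no | no |
| 12, Procedures | active and sham devices | no | no | no |
| 14, Consent | telephone screening, eligibility, consent | no | no | no |
| Appendix 8 | participant blinding to allocation | no | no | no |

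The group sizes agree with the total: 20 + 20 = 40. The protocol gives no alpha, power, effect size or SD, so there is no stated power figure to reproduce.

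**Step 2. What an imbalance could do (illustration).** From the protocol: n = 20 per arm. Assumed: two-sided alpha 0.05, no treatment effect, complete data, a continuous outcome with SD 1, and an imbalance b = 0.3 SD. The baseline-to-outcome correlation r is assumed to be 0.6, 0.7 or 0.8. Section 13b plans half-SD responder counts and chi-square tests, so a comparison of means serves only to give scale.

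The noncentrality is λ = (b/s) / √(2/20), where s is the residual SD. The rejection rate is the two-tailed probability from the noncentral t distribution.

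*(a) No baseline adjustment.* s = 1 and df = 38. λ = 0.3 / 0.3162 = 0.949, and the rejection rate is 15.2%.

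*(b) Baseline adjustment, with a stable baseline difference.* The arms differ by 0.3 SD at baseline and by the same amount at outcome. Adjustment leaves a bias of 0.3(1 − r), with s = √(1 − r²) and df = 37.

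*(c) Baseline adjustment, with the full 0.3 SD remaining.* The bias stays at 0.3, with the same s and df. This requires an imbalance in something the baseline score does not capture.

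| r | s | (b) bias left | (b) λ | (b) rate | (c) λ | (c) rate |
|---|---|---|---|---|---|---|
| 0.6 | 0.800 | 0.12 | 0.474 | 7.5% | 1.186 | 21.1% |
| 0.7 | 0.714 | 0.09 | 0.399 | 6.7% | 1.328 | 25.3% |
| 0.8 | 0.600 | 0.06 | 0.316 | 6.1% | 1.581 | 33.8% |

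The rates in (c) rise with r because the bias is held fixed while the residual SD shrinks.

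**Step 3. Other sizes of imbalance.** Unadjusted, by normal approximation, shifts of 0, 0.10, 0.25, 0.50 and 0.75 SD give 5.0%, 6.2%, 12.4%, 35.3% and 66.0%. The 0.50 SD value equals the minimally important difference in Section 13b. The documents do not say how large any real imbalance would be.

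**The case against.** **The label may simply be out of date.** The case-matched sentence also specifies abdominal and cervical spine treatment, whereas Section 6, Section 12 and Appendix 1 describe a helmet and nasal device. Section 6 carries a Stage 2 label, and the Background describes two stages. Sections 6, 8, 9 and 12 never mention matching. This largely stands as an explanation, and it means the protocol cannot be said to fix matching as the allocation method for these 40 participants. It does not remove the point. The sentence is current text about the Sydney trial with no stage limit, and if it is set aside no assignment method remains.

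**Matching and sham control can coexist.** True. The two labels are not mutually exclusive, and the problem is that neither comes with an assignment procedure.

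**Randomisation may be stated in text that could not be read.** The front matter and the text between Sections 6 and 8 were not available. The order of headings in Appendix 8 suggests that the latter covers study setting. This stands as a limit on certainty. If randomisation is stated there, the case-matched sentence still needs reconciling with it.

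**A stronger reading is tempting.** A reader might infer that staff who know the patients choose who receives light and who receives sham. No section says so. The reference to group allocations in Appendix 8 presupposes some allocation step, and recruiting two groups is ordinary wording. Silence on the method shows a missing safeguard, not selection by staff.

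**The larger false-positive rates are fragile.** This stands. The 21% to 34% range needs the whole 0.3 SD to persist after baseline adjustment, and the protocol plans no ANCOVA.

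**Conclusion.** The point holds as an inconsistency together with a missing safeguard. The design labels disagree, and no readable section provides random or concealed assignment. As written, the 20-versus-20 comparison is therefore not protected against selection bias. The documents do not show that bias is present or that assignment will in fact be non-random.

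The size is conditional. For an assumed 0.3 SD imbalance, the false-positive rate is about 15% unadjusted and about 6% to 7.5% when baseline adjustment removes most of a stable difference. It is 21% to 34% only in the extreme case in which adjustment removes none of it. These rates assume two-sided 5%, no treatment effect, complete data and r between 0.6 and 0.8. The conclusion on the text does not depend on them.

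Confidence is moderate because some pages could not be read.

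**What to change.** 1. In Section 2, remove case-matched or limit it explicitly to Stage 1. Reconcile that sentence with Section 6, including the treatment sites each names; the investigators must settle which description applies.
2. In Section 6, state that after consent and baseline assessment the 40 participants are randomised 1:1 from a computer-generated list.
3. State that allocation is concealed by coded device numbers, with the code held by someone already on the study who neither treats nor assesses participants.
4. Stratification by Hoehn & Yahr stage is optional. The stage is already established for eligibility in Section 8a, but with 40 participants the strata should be few to avoid sparse cells and incomplete blocks.

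This point requires no change of analysis model. If unreadable pages already state randomisation, steps 2 and 3 reduce to making Section 6 agree with them.

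The cost is a short amendment and preparation of the list, with no extra participants or visits. It has to be done before enrolment, because assignment cannot be repaired afterwards.
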